### Data Analysis

#### Sample size calculation

The sample size calculation is based on the proportional change in primary outcome measure (the FIM™) in the published My Therapy pilot study, which found that double the proportion of patients in the My Therapy group (22%) achieved a MCID in function (FIM) from admission to discharge, compared to usual care (10%) [24]. The sample size is based on a two-tailed alpha of 0.05, power of 0.99, as well as an intraclass correlation coefficient (ICC) of 0.005 (established from a previous rehabilitation study [20]). Using these parameters, the total sample size required is 2,160 patients. With an average of 25 beds per ward, length of stay of 18.5 days [45] and a data collection period of 54 weeks, each rehabilitation ward will contribute around 485 patients. Allowance has been made for this to be reduced to 340 when an opt-out rate of 30% is assumed. If each of the eight rehabilitation wards contributes 340 patients across the 54 weeks of data collection, the total of 2,716 will exceed the sample size requirement for the primary outcome measure of the proportion of people who achieve a MCID in FIM™. The sample size calculation allows for additional planned bed closures over the Christmas period and censoring of patients already admitted to the ward at the point of transition from the control to the experimental period, as these patients will be exposed to both conditions and will be censored to avoid data contamination.

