#### Statistical analyses

Analyses will only include data from patients who were admitted and discharged during the ward’s control condition period or experimental condition period. Patients still admitted to the rehabilitation wards at the end point of the study will not be included. It is expected that due to the step-wedged design, this will equally exclude long-stayers in the control and experimental condition periods. Each analysis will use individual patient-level data, clustered within the ward, and will use the length of time (in weeks) of experimental exposure as an effect modifier [32]. Length of time of exposure to the experimental condition is an important consideration when an intervention may take time to settle into usual practice and where there may be a cumulative effect [32]. Analyses will be conducted on an intention-to-treat basis.

The analyses will compare the FIM™ and the health-related quality of life utility index score between the control and the intervention groups. Health-related quality of life scores from the EQ-5D-5L will be converted from raw scores to a utility index based on an Australian population [46, 47]. The proportion of people who achieve a MCID of 22 points in FIM™ [35, 37] will be analysed using mixed effects logistic regression, and the change in FIM™ score and utility index will be ana-lysed using mixed effects linear regression. Length of stay will also be analysed via a linear regression model.

While not powered for a secondary analysis, there will be an exploratory secondary analysis of the same outcome measures within each of the clusters and for the two home-based bed-substitution wards. Other secondary outcomes will be compared between groups using univariable analyses. All outcomes will be reported with 95% confidence intervals and analyses will assume a significance of *p* < 0.05.

For the economic evaluation, the primary outcome will be presented as cost-effectiveness and cost-utility analyses, reporting (i) the cost per MCID in FIM™ achieved; and (ii) the cost per QALY gained. Costs will include the rehabilitation length of stay, acute transfers within the rehabilitation stay and unplanned re-admissions within the 30 days post discharge. The QALYs will be calculated using the utility index scores.

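### The plan lets the effect of My Therapy vary with weeks of exposure but defines no single effect for the primary test or the ICERs

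*Protocol article*

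**What the plan says.** Under Statistical analyses, each analysis uses patient-level data clustered by ward and "will use the length of time (in weeks) of experimental exposure as an effect modifier". The reason given is that this matters where "an intervention may take time to settle into usual practice and where there may be a cumulative effect". The economic part of the data analysis section repeats the modifier for all its analyses.

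The primary outcome, the proportion reaching the 22-point MCID in FIM, "will be analysed using mixed effects logistic regression". Change in FIM and the utility index go to mixed-effects linear models. The same section also says: "Other secondary outcomes will be compared between groups using univariable analyses". The modifier is therefore best read as applying to the primary, main secondary and economic models.

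The sample size rests on one contrast from the pilot, in which "double the proportion of patients in the My Therapy group (22%) achieved a MCID in function (FIM) from admission to discharge", against 10% under usual care. It uses a "two-tailed alpha of 0.05, power of 0.99" and an "intraclass correlation coefficient (ICC) of 0.005", and gives 2,160 patients. Each ICER is a single ratio, and cost per QALY is judged against a $50,000 threshold.

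**The concern.** Once exposure modifies the effect, there is a different effect of My Therapy at each week since crossover. Three parts of the plan need one effect: the sample size, the primary test and the ICERs. The article does not say at which exposure, or over what average, that effect is read.

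This goes beyond a coding detail. The article commits the primary analysis to a varying effect and gives its reason, but leaves open the quantity the trial tests. The two most obvious ways to extract one number are the condition coefficient from an uncentred interaction model and a single constant effect. Both fall short of the average effect if the programme builds up in the way the article anticipates. If the choice were made after the exposure curve had been seen, the same data could support different conclusions on effectiveness and cost-effectiveness.

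**Working it through.** **Inputs from the article.** Eight wards, nine six-week blocks, 10% v 22%, two-sided alpha 0.05, ICC 0.005, 2,160 patients.

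**Assumptions.** One ward crosses per step and block 1 is all control (inferred from eight wards and nine blocks; the timeline figure is not shown). Ward-blocks are equal in size, 2,160/72 = 30 patients. Calendar block is adjusted for as a category. Exposure is counted for the ward at block midpoints (3, 9, ... 45 weeks). A linear-probability approximation stands in for the logistic model, and no patients are lost around crossover.

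**Spread of exposure.** Successive exposure blocks hold 8, 7, 6, 5, 4, 3, 2 and 1 wards, 36 intervention ward-blocks in all. Mean exposure = (8×3 + 7×9 + 6×15 + 5×21 + 4×27 + 3×33 + 2×39 + 1×45)/36 = 612/36 = 17 weeks. Only three, two and one wards supply weeks 31-36, 37-42 and 43-48.

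**Model for ward-block means.** Mean = block effect + θ·(condition) + δ·(condition × weeks) + ward effect + error. Total variance is 0.16 × 0.84 = 0.1344. Ward variance is 0.005 × 0.1344 = 0.000672. Error variance per ward-block mean is 0.995 × 0.1344/30 = 0.00446. Estimation is by generalised least squares, with power = Φ(effect/SE − 1.96).

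**The plan's own figure.** With δ = 0, the SE is 0.0239 and power is Φ(0.12/0.0239 − 1.96) = 0.999. This is consistent with the stated 0.99, although the article does not show its formula. The same model reaches 99% power at 21 per ward-block, or 1,512 patients.

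**Flat 12-point effect, interaction model.** Var(θ + δw) = Var(θ) + 2w·Cov(θ,δ) + w²·Var(δ), with Var(θ) = 6.367×10⁻⁴, Cov(θ,δ) = −9.669×10⁻⁶ and Var(δ) = 1.413×10⁻⁶.

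| Effect read at | SE | Power |
|---|---|---|
| Week 0 | 0.0252 | 0.997 |
| Week 17 (mean) | 0.0268 | 0.994 |
| Week 24 | 0.0314 | 0.969 |
| Week 48 | 0.0544 | 0.60 |

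Even when the true effect is constant, power depends on where the effect is read.

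**Effect that builds up.** The article gives no build-up rate, so this is a range. Let a share f of the plateau effect be present at crossover, rising linearly to the plateau. Each curve is scaled so that its average over the 36 ward-blocks is 12 points. The week-0 column is the condition term from the uncentred linear interaction. The last column is the single effect from the model with δ = 0.

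| f | Plateau (weeks) | Week-0 term, % of average | Its power | Constant-effect model, % of average |
|---|---|---|---|---|
| 0 | 12 | 57 | 0.77 | 75 |
| 0 | 24 | 24 | 0.20 | 55 |
| 0 | 48 | 0 | 0.05 (two-sided false-positive rate) | 40 |
| 0.5 | 12 | 81 | 0.97 | 89 |
| 0.5 | 24 | 71 | 0.92 | 83 |
| 0.5 | 48 | 74 | 0.94 | 84 |
| 0.75 | 12-48 | 87-91 | about 0.99 | 92-95 |
| 1 (flat) | – | 100 | 0.997 | 100 |

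The case f = 0 with a 48-week plateau is extreme. It implies 12 × 45/17 = 31.8 points in the last exposure block.

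Under build-up from zero, the effect at mean exposure from the same interaction model returns 102%, 102% and 100% of the average for the three plateaus, with power about 0.99.

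**The case against.** A reader might infer that the plan's primary treatment term is the effect on the day of crossover, and that power therefore collapses. The article does not support that. It says only that exposure is an effect modifier and fixes neither a linear term, nor uncentred coding, nor a test of one coefficient. Categorical exposure, centred weeks or a marginal contrast would all satisfy the same sentence, and an analysis plan not shown may settle the matter. It would likewise go too far to say that the ICER denominators come from the start-up phase.

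The large losses also need an effect that starts from zero, and the article points away from that. Staff are trained and local strategies are designed in the six weeks before crossover, patients who straddle crossover are excluded, and My Therapy begins at the start of the admission. With half or more of the effect present at crossover, the loss of power is small. With a flat effect, the week-0 term is slightly more powerful than the average (0.997 v 0.994). Allowing the effect to vary is not an error in itself.

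These points stand, and they limit the size of the problem. They do not supply the missing definition. Describing the comparison as one between control and intervention groups does not say which value of a varying effect is meant.

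Two points bear on the remedy. Centring weeks at their mean gives the averaged difference in a linear model, but not the averaged risk difference in the logistic primary model. The average over observed exposure is also weighted towards early weeks by the rollout, so a mature-programme effect would be a legitimate alternative if named in advance.

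**Conclusion.** The concern holds in this form: the primary, main secondary and economic models make the effect depend on weeks of exposure, and no single effect is defined for the test at p < 0.05 or for the ICERs, although the trial is sized on one contrast.

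The consequence is conditional. Under default uncentred linear coding, the condition term recovers between none and all of a 12-point average effect, depending on how much of the effect is present at crossover. Its power runs from the false-positive rate to 0.997. Falling back on a constant effect is not a safe default either, since it recovers 40-75% under build-up from zero. These figures rest on the assumed build-up curves, one ward per step, equal ward-blocks, block adjustment and the linear-probability approximation. The gap in definition does not depend on them. The change is worth making because it settles what is tested and costs almost nothing.

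**What to change.** In the Statistical analyses section, and again in the economic text, state that the primary effect, and the effect entering each ICER, is the average over the observed intervention exposure. For the logistic primary model, obtain it from the exposure-time model by marginal standardisation: predict each intervention patient's risk with My Therapy at the ward's actual exposure and without it, then average the differences. Do not read it from the condition coefficient. Report the exposure curve as secondary, with a note that weeks beyond about 30 rest on three or fewer wards. Say also that the univariable secondary comparisons do not use the modifier.

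This takes a few sentences and no new data. If the effect is in fact constant, the standard error is about 0.027 instead of 0.024, and power is still about 0.99.

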### Outcomes

#### Clinical evaluation

The primary clinical outcome is *functional independence*, which will be assessed using the Functional Independence Measure (FIM™) [37, 38]. The change in FIM™ from admission to discharge will be reported as the pro-portion of patients who achieve a MCID in FIM™ (22 points) [37]. The FIM™ is routinely recorded on admission and discharge from rehabilitation by accredited assessors, and will be used to report an overall score and sub-categories of motor and cognitive function.

Secondary outcomes include change in *health-related quality of life*, assessed using the EQ-5D-5L [39]; *rehabilitation length of stay*, reported as the number of overnight stays between the rehabilitation admission and discharge dates; *days at home up to 30 days after surgery (DAH30)* for any surgical patients [40, 41]; hospital re-admissions to the same health service one month (30 days) post-discharge (yes/no); discharge accommodation, categorised as home, transitional care, residential care, hospital, or death (no accommodation); need for post-discharge rehabilitation services (yes/no); and adverse events (falls), assessed as the number of falls and the number of serious falls during the rehabilitation admission, and these will be classified as occurring during or not during My Therapy participation.

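### The FIM and utility models name no admission score as a covariate; adding it would sharpen the linear models and protect the primary one against baseline imbalance

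*Protocol article*

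**What the plan says.** Under Outcomes, Clinical evaluation, the primary outcome is a dichotomised change score: "The change in FIM™ from admission to discharge will be reported as the pro-portion of patients who achieve a MCID in FIM™ (22 points"). The same paragraph confirms that the starting value is available: "The FIM™ is routinely recorded on admission and discharge from rehabilitation by accredited assessors". For quality of life there is no equivalent statement. An admission EQ-5D-5L is only implied, because the outcome is a change.

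Under Data Analysis, Statistical analyses, the primary model is given as follows: "The proportion of people who achieve a MCID of 22 points in FIM™ [35, 37] will be analysed using mixed effects logistic regression". Mixed linear models are then planned with the FIM change and the utility change as responses. The terms given for each analysis are that the data are "clustered within the ward, and will use the length of time (in weeks) of experimental exposure as an effect modifier". The paragraphs on the economic analysis repeat these terms. No admission score, diagnosis or other patient covariate is named, and none is excluded. Only the remaining outcomes are called unadjusted: "Other secondary outcomes will be compared between groups using univariable analyses".

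**The concern.** Change from admission is not independent of the admission score. Patients who start low tend to gain more, and on a scale with a maximum (assumed here; the article gives no range) a patient with fewer than 22 points of room cannot be a responder under either condition. If admission FIM differs between control and experimental patients, a comparison of change, or of 22-point gains, carries part of that difference into the treatment effect.

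Randomisation does not secure balance in admission scores here:

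- Only eight wards are randomised, and any rehabilitation diagnosis is eligible (Design; Setting and participants).
- Patients are not blind to condition and may opt out after admission to a ward whose condition is already set. The Sample size calculation allows for 30% opting out.

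Two things are at stake: precision in the linear models, and residual confounding by starting function in all three models. Naming the covariate beforehand also prevents a later choice between adjusted and unadjusted results in an open-label trial.

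**Working it through.** **Inputs.** From the article: 10% against 22% responding, two-sided alpha 0.05, power 0.99, ICC 0.005, total 2,160, eight wards and nine blocks (so 2,160 / 72 = 30 patients per ward-block). Not in the article: the admission-discharge correlation rho and the SDs. These are assumed: rho of 0.5, 0.7 or 0.8, with equal SDs.

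**1. The plan's own power.** With the Hussey-Hughes variance, one ward crossing per step and 30 patients per ward-block:

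- Average-proportion variance: SE of the risk difference 0.0239. 0.12 / 0.0239 − 1.96 = 3.06, power 0.999.
- Intervention-arm variance: SE 0.0270. 0.12 / 0.0270 − 1.96 = 2.48, power 0.994.

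The stated 0.99 is met, so the primary analysis has little power left to gain.

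**2. Linear models: precision.** With common SD s, and before ward and period terms:

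- Change score: residual variance 2s²(1 − rho).
- Adjusted for admission score: s²(1 − rho²).
- Ratio, adjusted to change: (1 − rho²) / [2(1 − rho)] = (1 + rho) / 2.

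| rho | Ratio | Variance saved | Equivalent extra patients (1/ratio − 1) |
|---|---|---|---|
| 0.5 | 0.75 | 25% | 33% |
| 0.7 | 0.85 | 15% | 18% |
| 0.8 | 0.90 | 10% | 11% |

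Over a wider range the ratio runs from 0.65 (rho = 0.3) to 0.95 (rho = 0.9).

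If the SDs differ, let k be the discharge SD divided by the admission SD. The saving, in units of the admission variance, is (1 + k² − 2·rho·k) − k²(1 − rho²) = (1 − rho·k)². This is never negative, and it is zero only when rho·k = 1, for example rho = 0.8 with k = 1.25.

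**3. Linear models: imbalance.** With equal SDs, change regresses on the admission score with slope −(1 − rho). An illustrative imbalance of 0.2 SD therefore shifts mean change by 0.2 × (1 − rho) = 0.10, 0.06 or 0.04 SD at rho = 0.5, 0.7 or 0.8. Differencing removes the fraction rho of the imbalance and leaves the rest.

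**4. Adjusted change or adjusted discharge score.** If D − A = α + βx + γA, then D = α + βx + (γ + 1)A, where D is discharge score, A admission score and x condition. The treatment coefficient β is the same, so change can stay as the response.

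**5. Primary logistic model.** Simulation of 8 wards × 9 blocks × 30 patients, 10% against 22%, ICC 0.005, fixed ward and block effects, 200 replicates, for three assumed correlations between admission score and change:

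| Correlation | Log OR (SE), unadjusted | Log OR (SE), adjusted | Mean abs. z | Power |
|---|---|---|---|---|
| 0 | 0.937 (0.217) | 0.937 (0.217) | 4.31 to 4.31 | 0.985 to 0.985 |
| −0.3 | 0.937 (0.216) | 0.981 (0.222) | 4.32 to 4.42 | 0.990 to 0.990 |
| −0.5 | 0.949 (0.216) | 1.079 (0.232) | 4.38 to 4.64 | 0.995 to 1.000 |

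The SE of the log odds ratio rises or stays the same. The test gains slightly, by (4.42/4.32)² = 1.05 and (4.64/4.38)² = 1.12 in information, because the conditional odds ratio is larger.

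As a cross-check on step 2, the linear-model SE in the same runs fell from 0.075 to 0.065 at −0.5. That is a variance ratio of 0.75, as expected: with equal SDs a correlation of −0.5 between admission score and change corresponds to rho = 0.5.

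**The case against.** The strongest objection is that the article is silent rather than wrong. It names model families, clustering and an effect modifier; it neither lists nor excludes covariates, and a covariate list is commonly left to a fuller plan that is not shown. A reader might infer that the primary and continuous models are unadjusted by design. The text does not support that: only the other secondary outcomes are called univariable, and a change-score model can carry the admission score as a covariate. This part stands. What remains is that the article does fix change from admission as the response and does state the terms each analysis uses, with the most obviously useful covariate absent although it is recorded.

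A reader might also infer that the primary analysis loses precision without adjustment. It does not in the usual sense: the SE of the log odds ratio does not fall, planned power is already 0.99, and adjustment changes the estimand to a conditional odds ratio.

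Nor is case mix left wholly uncorrected. Every ward contributes patients under both conditions, analyses are clustered by ward, and differencing removes part of any imbalance. Nothing in the article shows that opting out differs by condition; the design merely permits it. Adjustment also cannot turn a patient without 22 points of room into a responder, since that limit belongs to the outcome definition.

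Finally, admission EQ-5D-5L is implied rather than stated, and diagnosis is not listed as a recorded variable. Both objections stand and limit the fix.

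**Conclusion.** The point holds as a recommendation to name the admission score in these models. It is not a demonstrated error.

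- **Linear models for change in FIM and utility:** the gain is real, at 25%, 15% or 10% of variance for rho of 0.5, 0.7 or 0.8. It rests on an assumed correlation and equal SDs and leaves out ward and period terms. Asymptotically, adjustment is never less precise than unadjusted change. It also removes the share (1 − rho) of any admission imbalance that differencing leaves.
- **Primary logistic model:** the benefit is mainly protection against imbalance in admission FIM. The gain in test power is small and the SE of the log odds ratio is no smaller. The size of any actual imbalance is unknown; the 0.2 SD above is only an illustration.

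**What to change.** In the Statistical analyses section, or in the analysis plan before outcome data are examined:

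1. Include admission FIM as a continuous covariate, with a spline or quadratic term, in both the model for the 22-point gain and the model for change in FIM.
2. Include admission utility in the model for change in utility index, and state that the EQ-5D-5L is collected at admission.
3. Keep change as the response or use the discharge score, as preferred; with the admission score in the model the treatment estimate is the same.
4. Because the adjusted odds ratio is conditional, also report a standardised risk difference for the primary outcome.
5. Add diagnosis group only if it is recorded.

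For FIM the cost is wording alone, since the admission value is already recorded. For utility it is also wording alone, provided the implied admission EQ-5D-5L is collected. No change to sample size or trial conduct is needed.

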To differentiate My Therapy from general therapist advice and education regarding self-practice during inpatient rehabilitation and goal setting with the patient, My Therapy must also adhere to the following criteria (a) a written program, (b) therapist documentation of the program within the medical record, (c) include a feedback mechanism to the therapist (e.g., a paper based or smart device tick sheet), and (d) be actively monitored and progressed as clinically required. My Therapy is tailored to individual needs, recommended by the patient’s treating occupational therapist and physiotherapist after goal setting with the patient, and can be practiced within business hours, in the evenings or over the weekend.

A recent pilot study showed the implementation of My Therapy to be feasible in hospitalised older people with musculoskeletal conditions and frailty (n = 116) [24]. The pilot study led to around 100 min of extra weekly practice alongside usual care rehabilitation and the benefits occurred without additional staff or adverse events [24]. Compared to usual care, more than double the proportion of patients allocated to My Therapy achieved a minimal clinically important difference (MCID) in functional independence from admission to discharge [24], and it was also delivered safely in those with cognitive impairment.

The current protocol builds on this initial pilot study [24]. The project will scale-up implementation of My Therapy across inpatient and home-based rehabilitation wards in Australian public and private health networks, and evaluate the benefits and cost-effectiveness of My Therapy via a stepped-wedge cluster randomised trial design. This trial aims to determine the effectiveness of My Therapy on clinical outcomes of function and health-related quality of life, when implemented across four health networks. It will also determine the cost-effectiveness per MCID in functional independence achieved and per quality adjusted life year (QALY) gained compared to usual care; in addition to the cost of implementation. We hypothesise that My Therapy will result in improved functional independence and health-related quality of life during rehabilitation without adverse events (falls); and will be cost-effective to the health service due to a reduction in rehabilitation length of stay, compared to usual care alone.

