### Setting and participants

The project will take place within eight rehabilitation wards (totalling over 200 rehabilitation beds) across four Victorian health networks (see anzctr.org.au for study sites). At one health service, the two wards will incorporate home-based bed-substitution; all others will be located within inpatient facilities. We will include all patients aged 18 years or older undergoing rehabilitation on the selected rehabilitation wards during the trial period, of any rehabilitation diagnosis. Patients who do not speak English and those with a cognitive impairment will not be excluded. We will exclude any patients without coverage under Australia’s universal health care program (Medicare).

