### Data collection and management

All data, including the primary outcome, will be obtained from medical records, hospital incident reporting systems, or via hospital costing units. Study data will be collected and managed using REDCap (Research Electronic Data Capture) electronic data capture tools hosted at Monash University and managed by Helix [42, 43]. EDCap is a secure, web-based application designed to support data capture for research studies, providing (1) an intuitive interface for validated data entry; (2) audit trails for tracking data manipulation and export procedures; (3) automated export procedures for seam- less data downloads to common statistical packages; and (4) procedures for importing data from external sources. On each ward, a designated allied health assistant, employed by the health service will enter data from participants’ medical record into a custom-built REDCap database. The site coordinator will review the accuracy of the study data from a random selection of 20% of participants each week. The site coordinator will randomly sample based on the availability of the medical records at the time of data review.

Every six weeks, each site’s coordinator will extract data recorded about falls from the hospital reporting system. Falls data will be reviewed by the Independent Data Safety and Monitoring Committee (DSMC) [44]. The DSMC will comprise of two experienced independent researchers who have no vested interest in the outcome of the trial and they will remain blind to ward allocation. We have prespecified a falls event rate *>* 10% over the normal upper limit, based on 12 months of historical falls data from the participating wards, as requiring intervention by the trial steering committee. Any harm suffered from participation in the trial will be managed by the health service who provided rehabilitation care.

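### The univariable plan for the remaining secondary outcomes omits calendar period, contradicts the ward-clustering statement, and leaves falls without time at risk

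*Protocol article*

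**What the plan says.** The Statistical analyses section gives mixed-effects logistic regression to the FIM responder outcome, mixed-effects linear regression to FIM change and the utility index, and a linear regression to length of stay. It then says: "Other secondary outcomes will be compared between groups using univariable analyses". Set against the outcome list under Clinical evaluation, what remains is DAH30 for surgical patients, 30-day readmission, discharge accommodation, post-discharge rehabilitation services, falls and serious falls. These comparisons are inferential: "All outcomes will be reported with 95% confidence intervals and analyses will assume a significance of" p < 0.05.

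Earlier, the same section makes a general statement: "Each analysis will use individual patient-level data, clustered within the ward". It adds that each analysis "will use the length of time (in weeks) of experimental exposure as an effect modifier". The Methods paragraph of the Abstract likewise describes mixed-effects linear or logistic models for the clinical outcomes, without exception. Calendar period is not named as a model term for any outcome.

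Falls are "assessed as the number of falls and the number of serious falls during the rehabilitation admission", with no denominator. The Background expects cost-effectiveness "due to a reduction in rehabilitation length of stay". Under Data collection and management, safety review has its own trigger: "We have prespecified a falls event rate" measured against 12 months of historical ward data.

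**The concern.** In a stepped wedge every ward moves from control to intervention, so condition and calendar time are confounded by design. Randomising the crossover order does not remove this. A comparison containing condition alone attributes any secular change in readmission, discharge destination or falls to My Therapy. The protocol itself names one calendar-linked change, the Christmas bed closures. Weeks of exposure do not fill the gap: they are zero for every control patient, so they carry no information on a trend under usual care.

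Ward matters as well. Early-crossing wards supply most intervention patients and late-crossing wards most control patients. The wards also differ in kind: "At one health service, the two wards will incorporate home-based bed-substitution; all others will be located within inpatient facilities". Discharge destination, falls and readmission could plausibly differ between those two wards and the rest.

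At stake are the outcomes that show whether earlier discharge shifts burden elsewhere, and falls, the only adverse event named in the trial's hypothesis. If stays shorten, falls per admission go down even when the daily risk of falling is unchanged or higher.

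**Working it through.** **Inputs.** From the protocol: 8 wards, nine six-week blocks, N = 2,160, ICC 0.005, 10% v 22%, two-sided 0.05, power 0.99, mean stay 18.5 days. Assumptions: one ward crosses per step (the timeline figure is not shown) and cells are equal, so 2,160/72 = 30 patients per ward-block.

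**1. The plan's own figure.** The protocol gives no figure for the univariable comparisons, so the sample size serves to check the layout. The Hussey–Hughes variance has a ward random effect and period fixed effects:

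Var = Iσ²(σ² + Tτ²) / [(IU − W)σ² + (U² + ITU − TW − IV)τ²], with I = 8, T = 9, U = 36, W = V = 204.

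The two brackets are 288 − 204 = 84 and 1,296 + 2,592 − 1,836 − 1,632 = 420. For 10% v 22%, p̄(1−p̄) = 0.1344, τ² = 0.000672 and σ² = 0.995 × 0.1344/30 = 0.00446. The SE is 0.0239 and power is 0.999. For an exact doubling (10% v 20%) power is 0.990, and 30 per cell is the smallest size that reaches 0.99. The layout therefore agrees with the stated N.

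**2. Calendar gap.** Ward i is in control for blocks 1 to i. There are 36 control and 36 intervention cells. Mean block is 120/36 = 3.33 for control and 240/36 = 6.67 for intervention. The gap is 3.33 × 6 = 20 weeks.

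**3. If ward is ignored, no trend.** Ward i supplies (9−i)/36 of intervention patients and i/36 of control patients. The squared differences sum to 2(49 + 25 + 9 + 1)/1,296 = 168/1,296 = 0.130. The true variance divided by the variance the crude test assumes is

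1 − ICC + 0.130 × ICC/(4/2,160) = 1 + 69 × ICC,

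and type I error = 2Φ(−1.96/√ratio).

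| ICC | Variance ratio | Type I error |
|---|---|---|
| 0.005 (protocol) | 1.345 | 9.1% |
| 0.02 (assumed) | 2.38 | 20% |
| 0.05 (assumed) | 4.45 | 35% |

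**4. With a secular trend.** Simulation under no treatment effect, ICC 0.005, 30 per cell, assumed 15% event rate at the start, log-odds drifting linearly over the nine blocks (1,500 runs per row, Monte Carlo error about 1 point):

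| Assumed OR over trial | Condition only | Ward, no period | Ward and period | Spurious difference |
|---|---|---|---|---|
| 1.0 | 8.5% | 4.7% | 4.9% | 0 |
| 1.25 | 17% | 14% | 4.1% | 1.3 points |
| 1.5 | 36% | 42% | 4.5% | 2.5 points |
| 2.0 | 73% | 87% | 4.7% | 4.6 points |

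Hand check at OR 1.5: the drift between the mean blocks is log(1.5) × 3.33/8 = 0.169. Multiplied by p(1−p) = 0.146 at a mid-trial risk of 17.8%, this gives 2.5 points. At an assumed 30% event rate, ward without period gives 22% (OR 1.25) and 59% (OR 1.5).

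**5. Falls.** Hold the rate per bed-day constant and shorten the stay from 18.5 days by an assumed 1, 2 or 3 days. Falls per patient change by 17.5/18.5, 16.5/18.5 and 15.5/18.5, which are drops of 5%, 11% and 16%. Conversely, equal falls per patient would conceal a rate per bed-day higher by 18.5/17.5 = 1.06, 18.5/16.5 = 1.12 or 18.5/15.5 = 1.19.

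**The case against.** A reader might infer that ward is certainly ignored. The document does not establish this. The general statement covers each analysis, and a model with condition as its only fixed effect plus a ward random effect can loosely be called univariable. What stands is a conflict between two sentences of one section, and step 3 applies under only one reading.

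A reader might also infer that the p-values are invalid outright. That is too strong. With ward modelled and no trend, error stays near 5%. The trend sizes, the event rates and the ICCs above 0.005 are assumptions. An illustration with the home-based wards has the same limit. If 95% of their patients and 75% elsewhere went home (assumed), the crude difference could reach (7 + 5)/36 × 20 = 6.7 points in either direction by crossover order. Averaged over random orders it is zero, so this is extra variance and not systematic bias.

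On falls, the definition does not forbid an offset, which could sit in an analysis plan, and the data safety committee's trigger already uses a rate. It would be wrong to infer that all falls monitoring is compromised. That trigger compares with historical data, however, and does not repair the comparison between conditions.

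Finally, the missing period term is not peculiar to these outcomes, since the primary model as written names none either. This affects how the remedy must be worded. It does not rescue a sentence that fixes a method with no place for period.

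**Conclusion.** The point holds in a conditional form. The protocol states a method for DAH30, readmission, discharge accommodation, follow-up rehabilitation and falls that has no term for calendar time, which the design confounds with condition. That method also contradicts the section's own clustering statement. Neither reading is adequate. Under the univariable reading, error is about 9% at the protocol's ICC even without a trend. Under the clustering reading, error is nominal without a trend but about 14–42% at an assumed secular odds ratio of 1.25–1.5 and a 15% event rate. Ward plus period gives about 5% in either case. For falls, the size depends on how far stays shorten: 6–19% of excess daily risk hidden for an assumed 1–3 days. All figures take one ward crossing per step and equal ward-block sizes. The primary outcome, FIM change, utility and length of stay are outside this sentence.

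**What to change.** Replace the univariable sentence. State that DAH30, 30-day readmission, discharge accommodation, post-discharge rehabilitation, falls and serious falls will each be analysed with a ward random effect and calendar-period fixed effects. Write the period term out: referring to the primary model would not supply it.

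- Readmission and follow-up services: mixed logistic regression.
- Discharge accommodation: multinomial model, or logistic for home v not home.
- DAH30: a mixed model suited to its distribution.
- Falls and serious falls: mixed Poisson or negative binomial regression with log(bed-days) as offset, reported as rate ratios with 95% confidence intervals.

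The cost is wording and a few more model fits; length of stay and all the outcomes are already collected. Intervals will be wider than the crude ones. Using the variance in step 1 at ICC 0.005, the ratio to the crude variance is 0.000571/(0.1344 × 4/2,160) = 2.29, so intervals are about 1.5 times as wide. That width reflects what the design can support once period is allowed for.
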